## Anticipated Results from Analysis of Microbiome and Metabolome

We will use multivariate ordination techniques to summarize and visualize the major trends in variation in microbial community composition of infants’ stool collected. The analyses will identify those taxa most closely associated with microbiome change through time. We will use canonical ordination to quantify the impacts of other covariates (diet, age, and interventions) on the microbiome composition. We will identify key microbial taxa in the ordination space that capture the trend in variation in relation to disease and use these with the results of the ordination as input variables for the subsequent mixed-effect and SEM analyses below. To ensure the results are not spurious, the observed differences in metabolomic profiles will be validated by permutation testing in MetaboAnalyst 3.0 (86). Where appropriate, significance of categorical variables were determined using the non-parametric Mann–Whitney test for two category comparisons or the Kruskal–Wallis test when comparing three or more categories (87) and all *p*-values were adjusted for multiple comparisons with the false discovery rate algorithm (88).

MixOmics (89) will be implemented to determine the correlation between the relative abundance of the dominant bacterial taxa from 16S rRNA gene sequencing and the intensity of metabolites of interest by sparse partial least squares regression (90). Longitudinal and network analyses will facilitate investigations into the directionality of any observations. Tax4Fun (62) will be used to infer the metabolic potential of the microbiome based on the 16S data. Model-based integration of metabolite observations and species abundances will then be applied to determine biologically feasible correlations between the inferred bacterial KEGG orthology and the resulting metabolites of interest (91). This will determine which metabolites are likely to be bacterial derived. It is important to note that in the course of data generation, new tools are likely to emerge that can perform distinct analyses on multi-omic data. Where appropriate we will incorporate such tools where they are likely to (1) outperform existing tools and/or (2) allow novel analyses to be performed.

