#### Necrotizing Enterocolitis

Necrotizing enterocolitis may be diagnosed at surgery, at postmortem or clinically and radiologically: at least one of the following clinical signs present: bilious gastric aspirate or emesis, abdominal distension, or occult or gross blood in stool AND at least one of the following radiological features: pneumatosis intestinalis, hepatobiliary gas, or pneumoperitoneum. Infants who satisfy the definition of NEC but at surgery or postmortem have a “focal gastrointestinal perforation” will not be coded as having NEC.

All diseased cases meeting the predefined case definition of NEC or LOS will have samples analyzed (expected total ~70–100 infants). Samples from up to 200 non-diseased cases will be selected to ensure sufficient coverage of intervention arms using matching algorithms and coverage of other clinical risk factors and outcomes. We will also analyze samples from non-diseased cases to determine microbiomic and metabolomic profiles between trials arms.

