### Quantifying the Direct and Indirect Impact of Risk Factors on Disease

We will use repeated measure mixed-effect modeling to quantify the direct effects of microbiome on risk of disease while adjusting for clinical factors. We will use case as the random effect and adjust for autocorrelation in the response using appropriate correlation structures in the model. The applicants have used this approach extensively to investigate the epidemiology of food-borne pathogens (92). We will use an SEM approach to quantify direct and indirect effects of risk factors on the incidence of disease. We will develop a set of models that characterize the relationship between clinical factors, the changes in gut microbial community types, developmental stage (postnatal and postmenstrual age), and comorbidities associated with disease onset and then challenge the model with the data derived from the laboratory and clinical data collection (93).

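### Taxa chosen for their relation to disease are then tested in models of that same disease, so the estimates and p-values for those taxa are biased away from the null by an amount that depends on how the choice is made

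*Protocol article*

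**What the plan says.** The section *Anticipated Results from Analysis of Microbiome and Metabolome* describes two linked stages. The first selects: "We will identify key microbial taxa in the ordination space that capture the trend in variation in relation to disease and use these with", and the sentence continues "the results of the ordination as input variables for the subsequent mixed-effect and SEM analyses below".

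The section *Quantifying the Direct and Indirect Impact of Risk Factors on Disease* gives the outcome of the second stage. For the mixed model: "We will use repeated measure mixed-effect modeling to quantify the direct effects of microbiome on risk of disease while adjusting for clinical factors". For the SEM: "We will use an SEM approach to quantify direct and indirect effects of risk factors on the incidence of disease". The SEM is to be developed, and the authors will "then challenge the model with the data derived from the laboratory and clinical data collection", which is the study's own material.

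Two safeguards appear in the first of these sections. Permutation testing is attached to differences in metabolomic profiles. False discovery rate (FDR) adjustment is given in the sentence on Mann–Whitney and Kruskal–Wallis tests. Neither is described as covering the step from taxon selection to disease model.

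**The concern.** If disease status helps decide which taxa enter a model, and the model then estimates the effect of those taxa on disease in the same infants, chance differences that favoured a taxon at selection count again at testing. Ordinary standard errors and p-values ignore the search, so coefficients come out too large and p-values too small. The same holds for SEM paths that run through the selected taxa.

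This matters because the plan wants more than description. *Aims and Objectives* frames the work as hypothesis testing, and *Statistical Analysis* intends to measure how far individual risk factors cause disease. A reader would take a small p-value for a named taxon in the final models as evidence about that taxon.

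**Working it through.** The article gives no figure for this step, so there is none to reproduce. The check is a simulation in which no taxon is related to disease.

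**Inputs from the article.** About 70 to 100 diseased infants (85 is the midpoint) and up to 200 non-diseased infants ("Samples from up to 200 non-diseased cases will be selected"), both from the section on the NEC case definition; two-sided 5% level, from *Sample Size Estimates*.

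**Assumptions, because the article is silent.** 30, 50 or 100 candidate taxa; five selected; normally distributed values; one record per infant; a linear model in place of the repeated-measures mixed model and SEM.

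**1. Independent taxa ranked by their association with disease, tested in the same infants**

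| Candidate taxa | Selected taxa with p<0.05 | At least one p<0.05 |
|---|---|---|
| 30 | 29% | 76% |
| 50 | 45% | 90% |
| 100 | 69–70% | 99% |

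A hand check agrees. The chance that at least one of m independent null taxa reaches 5% is 1 − 0.95^m: 78.5% for 30, 92.3% for 50 and 99.4% for 100. With 30 candidates, 0.05 × 30 = 1.5 are expected to be significant by chance, and 1.5/5 = 30% of the selected five. Five taxa fixed in advance would give 5% per taxon and 1 − 0.95^5 = 22.6% for at least one. Over a wider grid (20 to 100 candidates, 3 to 10 selected) the per-taxon rate ran from 11% to 88%. Using 70 or 100 cases changed little.

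**2. Correlated taxa.** One set of runs gave 12–15% per taxon and 40–46% for at least one. Another, with 50 candidates and correlation parameter 0.4, gave 23% per taxon. The figure moves with the strength and form of the correlation, which the article does not give.

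**3. Other readings of selection in the ordination space**
- Ordination constrained by disease: 14%, 24% and 30% per taxon for 20, 50 and 100 candidates.
- Unsupervised axes, with disease used only to choose the axis: 5–7% per taxon; overall model test 6.6–7.6%.
- Selection blind to disease: about 5% per taxon; overall test 4.8–6.4%.

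**4. Is reuse of the data the cause?** Selecting in one random half of the infants and testing in the other gave 4.3–5.5% per taxon in every setting.

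**5. Would FDR adjustment help?** Applied only to the five selected taxa, it still left a false discovery in 31%, 46% and 73% of runs for 30, 50 and 100 candidates. Applied to all candidates before selection, the rate was 3–6%.

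**6. Estimates (independent taxa, 50 candidates, five selected).** With no true effect, the selected taxa differed between cases and controls by 0.26 SD on average in absolute size. The standard error of one such difference is √(1/85 + 1/200) = 0.129 SD, so an unselected null taxon would average 0.80 × 0.129 = 0.10 SD. Model R² was 0.070, against 0.018 in fresh infants. With five taxa truly shifted by 0.3 SD, the selected taxa showed 0.35 SD against a true average of 0.18 SD.

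**The case against.** The strongest reply is that the article describes ordination, not univariate screening. Its canonical step lists diet, age and interventions as covariates, not disease, and the interim section uses unconstrained ordination to find the taxa that contribute most to community variation. If the team reads taxa off an unsupervised axis that happens to track disease, the inflation is close to nil (item 3). This stands as a limit on size. It does not remove the point, because the selection sentence ties the choice of taxa to disease in plain words and the more harmful readings fit it equally well.

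Secondly, this is a condensed article, and a validation step may be set out elsewhere. That selection and testing use the same infants is inferred from the absence of any split or second cohort. However, the two-stage rule itself is stated here, so this is more than an omitted detail.

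Three stronger readings are tempting but not supported:
- *All the model results are circular.* They are not. Clinical factors and ordination scores or community classes derived without disease status are not selected on the outcome.
- *The hypothesis of pre-disease microbiota differences is confirmed by construction.* *Aims and Objectives* gives it a direct comparison of up to seven daily pre-disease samples with control samples, which does not need the second-stage models.
- *The plan itself condemns this fault.* The *Summary* attributes type I error in earlier studies to residual confounding and reverse causation, not to selection followed by re-testing.

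**Conclusion.** The concern holds for the selected taxa and the SEM paths through them. Their coefficients are biased away from zero and their nominal p-values are too small, and neither stated safeguard reaches this step.

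The size cannot be fixed from the article. Under the assumptions listed, the per-taxon false-positive rate is about 29–70% for independent taxa ranked on disease, roughly 12–23% for correlated taxa, and 5–7% if disease only picks an unsupervised axis. The highest figures belong to the least favourable reading and should not be quoted alone. The exploratory setting softens the consequence but does not make these p-values valid as tests.

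**What to change.** Amend the selection sentence in *Anticipated Results from Analysis of Microbiome and Metabolome* in one of two ways:

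1. Choose the taxa that enter the disease models without using disease status, for example by loadings on unconstrained ordination axes or a fixed prevalence or abundance cut.
2. Keep disease-informed selection, but obtain p-values by permuting disease status at the infant level, respecting matched sets, and repeating selection and model fitting in each permutation. This corrects the p-values but not the size of the coefficients, which should still be described as selected estimates.

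If disease-informed selection is kept without option 2, report the taxon-level estimates and paths as descriptive only, without p-values presented as tests.

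The cost is some analysis code and fewer nominally significant taxa; no new samples are needed. Cross-fitting by infant is a further option but need not be required. At the article's 5–10% incidence, 480 infants give 24 to 48 NEC cases, or about 5 to 10 per fold if five folds were used.

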Volatile organic compounds from stool samples will be analyzed by GCMS using well-established protocols for extracting and analyzing headspace gases. These methods are based on a CARB/PDMS SPME fiber, a Combipal sampler with a Peltier-cooler, and a Perkin Elmer Clarus 600 Gas Chromatograph with Clarus 600T Mass Spectrometer (82). The method is validated on as little as 50 mg of sample: sufficient to analyze ~40 compounds, which includes 8 different acids, particularly SCFAs, branched and linear, alcohols, and esters. Interpretation of fragment patterns will be undertaken against the current mass spectral NIST library, followed by manual visual inspection (82).

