### Sample Size Estimates

Sample size requirements for each element of this study have been evaluated and are based on both published data and practical/logistical aspects from our existing work and that from other published studies. These considerations include
The duration, estimated start time, and recruitment rate for ELFIN, along with the estimated start date for MAGPIE and logistical issues in establishing recruitment from 10 hospital sites.The trial efficacy and disease event rate will not be known until the main trial completes. The incidence of NEC (Bell stage 2 or greater) is expected to be 5–10% and for LOS <20%, and some infants will have both diseases. Recruiting 480 infants will identify between 70 and 100 “disease” cases, 10–20 cases requiring gut surgery, and provide well sampled “non-diseased” infants with varying clinical risk factors, exposures, and outcomes.VOC analysis may identify several individual compounds; in our recent paper publishing the methodology, we show that on average 31.3 ± 10.5 (mean and SD) VOCs were identified per sample (82). At a power of 80%, and two-sided significance at the 5% level, we would need 50 infants per trial intervention group to show an increase in 5 VOCs. The SD for each sample was 2.9 ± 1.3 compounds and on average 90% of the VOC abundances showed a coefficient of variation smaller than 30%. Our data also showed in a study of 13 infants, which VOC number in healthy neonates significantly increased with age (0.49 extra VOCs per day 95% CI 0.12–0.86), a trend not seen in those who developed NEC (64).Microbiomic data complexities means that the sample size necessary to evaluate the actions of different interventions and the incidence of disease is dependent on effect size, the number of interacting factors, and their correlation. For a power of 80% to detect a 50% difference in community profile patterns arising from a categorical descriptor of microbial community variation, using a two-sided test at a significance level of 5%, the study needs ~200 samples. In our previous studies (1) 12 twin pairs analyzed (gut microbial profiling) using PLS-DA showed highly significant correlations between pairs (53) and (2) examination of 136 samples from 32 patients (*n* = 20 NEC or LOS) showed significant differences (*p* = 0.002) in microbiomic patterns between diseased and healthy individuals (24).Using immunohistochemical data from our group (83), and assuming that any differences between disease and control will be greater than those in healthy individuals, and using a two-sample *t*-test, our proposed sample size of 20 would give 80% power to detect a difference of 0.66 (66%) in cells/crypt cross section at a significance level of 5% and an approximated SD of 0.5 (50%).Mixed-effects models, which we propose for modeling the direct effects of the microbiome on disease risk, are economical with power because the residual variance of these models is smaller since some of it is accounted for in the random effect. Using the method by Cohen (84), we calculate that a GLM would have a power of 82% with 10 predictors and 50 for a “large” effect size (*f*^2^ = 0.35, *R*^2^ = 0.51) at the 5% level of significance, and a power of 47% for a “medium” effect size (*f*^2^ = 0.15, *R*^2^ = 0.36) at the 5% level of significance. With *n* = 100 the calculated powers are 99% for a large effect size and 74% for a medium effect size. Including random effects in the GLM would increase power at the same effect size or conversely permit smaller effect sizes at the same power. The power analysis of an SEM is altogether more complex because it relies on the goodness-of-fit criteria selected for the model. Power at the model level may be low when there are few model degrees of freedom even for a reasonably large sample size; requiring greater than 100 samples if there are fewer than 20 model degrees of freedom (85). We will supplement these models where needed using a Bayesian SEM approach.

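### The VOC-number comparison is sized at an unadjusted 5% level, but the analysis text FDR-adjusts tests of this type without exempting it, so the printed 80% power is not that of the planned test

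*Protocol article*

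**What the plan says.** Two comparisons in Sample Size Estimates are sized as single tests at 5%.

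- **VOC number.** "At a power of 80%, and two-sided significance at the 5% level, we would need 50 infants per trial intervention group" to show a difference of 5 VOCs. The spread is given just before: "on average 31.3 ± 10.5 (mean and SD) VOCs were identified per sample".
- **Microbial community.** For a 50% difference in a categorical descriptor of the community, "using a two-sided test at a significance level of 5%, the study needs ~200 samples".

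Neither calculation mentions multiplicity.

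Anticipated Results from Analysis of Microbiome and Metabolome says that, where appropriate, two categories are compared by Mann–Whitney and three or more by Kruskal–Wallis. The sentence ends: "all *p*-values were adjusted for multiple comparisons with the false discovery rate algorithm". It gives no FDR level and no family, and it sets no comparison apart.

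Other sections show how many tests might sit beside the VOC count. The headspace method is described as "sufficient to analyze ~40 compounds" (Laboratory Procedures—Stool and Urine). Aims and Objectives lists four sampling windows and Procedures—Summary lists five, with about 25–50 infants per arm.

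**The concern.** A two-arm comparison of VOC number is the kind of test to which the FDR sentence applies. If it is adjusted together with anything else, such as the same count at other time windows or the individual compounds, it usually needs a raw p-value below 0.05 to be declared significant. A sample size computed at 5% then overstates its power.

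The practical risk is a null result on VOC number being reported as coming from a test with 80% power when the rule actually applied gave it less. A few planned summary comparisons could also be diluted by a screen of many exploratory features. The article fixes both the error rule and the power figure, and the second takes no account of the first.

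**Working it through.** **Inputs.** From Sample Size Estimates: difference 5, SD 10.5, 50 per group, two-sided 5%, power 80%. From Laboratory Procedures—Stool and Urine: about 40 compounds. From Aims and Objectives: four windows. Assumed, because not stated: Benjamini–Hochberg, FDR level 5%, independent tests, and the shares of true effects shown below.

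**Step 1: the plan's own figure.**

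n per group = 2 × [SD × (1.960 + 0.842) / difference]² = 2 × (10.5 × 2.802 / 5)² = 2 × 34.6 = 69.2, so 70 (the t-test also gives about 70).

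The printed 50 is not reproduced. A one-sided test gives 55, a paired design 35, and the other printed SD of 2.9 gives 6. Fifty per group would need an SD of about 8.9 or a difference of about 5.9.

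Power at 50 per group: 5 / (10.5 × √(2/50)) = 5 / 2.1 = 2.381, and Φ(2.381 − 1.960) = 66% (t-test 65%).

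**Step 2: effect of the FDR step.** With m tests, Benjamini–Hochberg rejects the k smallest p-values for the largest k at which the k-th is at most 0.05 × k/m. The strictest threshold is 0.05/m.

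- m = 4: threshold 0.0125, z = 2.498. A test built for 80% keeps Φ(2.802 − 2.498) = 62%. The VOC test as printed has Φ(2.381 − 2.498) = 45%.
- m = 41 (40 compounds plus the count): threshold 0.00122, z = 3.234. The corresponding values are 33% and 20%.

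These are lower limits, because other rejections relax the threshold. Simulated power (40,000 replicates, every true effect of equal size):

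| Tests | True effects | Test built for 80% | VOC count as printed |
|---|---|---|---|
| 1 | 1 | 80% | 66% |
| 4 | 1 | 63% | 46% |
| 4 | 4 | 77% | 60% |
| 41 | 1 | 34% | 20% |
| 41 | 4 | 43% | 25% |
| 41 | 20 | 66% | 44% |
| 41 | 41 | 77% | 58% |

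**Step 3: detectable difference for a screened feature.** This uses the two-sample t-test at 80% power. The thresholds are illustrative; two rejections among 41 tests, for example, give 0.05 × 2/41 = 0.0024.

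| Per arm | p < 0.05 | p < 0.0025 | p < 0.001 |
|---|---|---|---|
| 50 | 0.57 SD | 0.79 SD | 0.85 SD |
| 25 | 0.81 SD | 1.15 SD | 1.24 SD |

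**Step 4: the community comparison.** The ~200 samples cannot be recomputed, because the 50% difference has no stated base. The methods named for community composition are ordination and canonical ordination (Anticipated Results), mixed models and structural equation models (Quantifying the Direct and Indirect Impact of Risk Factors on Disease), and at the interim MANOVA against an unadjusted 0.05 (Plan for Interim Statistical Analyses). None of these is the Mann–Whitney or Kruskal–Wallis test to which the FDR clause is attached.

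**The case against.** The sized quantities are single summaries: one count of VOCs per sample and one categorical community descriptor. Neither is a test of a single compound or taxon, and FDR adjustment of a family of one changes nothing. No section pools the VOC count with the individual compounds, so the 41-test family is a construction. A natural reading is that FDR applies across many features while a named summary is tested at 5%. Defining families is commonly left to a statistical analysis plan, which is not shown.

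Much of this stands. It is why the loss is a range that starts at zero, and an unstated family would not by itself be a finding. What remains is that the article chose to state the rule, worded it to cover all p-values of these comparisons, and printed a power that ignores it. The interim section states an unadjusted criterion openly; the main analysis text does not do so for VOC number.

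The objection succeeds on the community comparison. A reader might infer that the ~200-sample figure loses its power in the same way. The documents do not support that, because they do not assign this comparison to the FDR-adjusted tests and mainly name other methods for it.

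It is also fair that the VOC power fails before any adjustment. That arithmetic error is separate from the FDR mismatch, and the two compound.

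**Conclusion.** The point holds for the VOC-number comparison. It was sized at an unadjusted 5% level, while the stated rule adjusts tests of its type and grants no exemption. Under Benjamini–Hochberg at 5% with independent tests, a nominal 80% is 80% for a family of one, about 63–77% for four tests and about 34–77% for 41. From the printed inputs the power is about 65–66% unadjusted, about 46–60% with four tests and about 20–58% with 41. The upper ends require every test in the family to have a real effect; the lower ends require only one.

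A reader might conclude that the power is roughly halved, or that no stated power survives. The documents do not support so flat a claim. Losses of that size arise only when the family is large and true effects are sparse, and neither condition is stated. For the community comparison the point is conditional on its being tested by Mann–Whitney or Kruskal–Wallis within a family of several tests.

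**What to change.** In Anticipated Results from Analysis of Microbiome and Metabolome, name the summary comparison for each platform (VOC number; the community descriptor) as a single test at 5% outside the FDR family. Apply FDR within each platform to the individual compounds, features and taxa.

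In Sample Size Estimates:

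- say that the 5%-level powers apply only to those named tests;
- restate the VOC figure as about 66% at 50 per group, because exempting the test without this correction would reaffirm an 80% that its inputs do not give;
- give the detectable difference for FDR-screened features, about 0.8 SD at 50 per arm and about 1.2 SD at 25 per arm, on the assumption that the effective threshold is about p < 0.0025 to p < 0.001.

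The cost is a few sentences and a less favourable stated figure. No infants or samples are added.
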